## Methods

### Study design and setting

This is a pragmatic, population-based, superiority, cluster-randomized trial with two intervention arms, of which one serves as comparator. The first arm (HDI) consists of a systematic screening followed by an individually oriented lifestyle-focused health dialogue based on the risk profile obtained from the screening. The second arm (OS) consists of opportunistic screening and represents the comparator. The PCCs represent the clusters and unit of randomization, while patients and healthcare professionals at the PCCs represent units of observation.

This trial will be conducted within primary health care in the Stockholm Region in Sweden. The Stockholm Region has the largest population of the 21 regions in Sweden. The region had a total of 2,440,027 (23.2%) inhabitants in 2022, of which 313,924 were aged 50–59 years old, according to official, publicly available data from Statistics Sweden. In Sweden, primary care is part of the tax-funded health system, which is governed and managed by the 21 regions, which includes both public and private PCCs. In 2022, there were a total of 231 PCCs in Stockholm Region, of which 67 were public and 164 were private. The public and private PCCs are funded and governed according to the same rules but differ in how they are organized and managed. Both public and private PCCs will be included in this trial. The target population is individuals living in areas of low socioeconomic status, and we will therefore select PCCs based on their Care Need Index (CNI). The CNI is a social deprivation index which describes the expected risk of ill health within a patient population, based on socioeconomic and demographic factors [18].

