### Sample size

Sample size calculations were based on change in systolic blood pressure as the main outcome measure. We considered a 5-mmHg reduction in systolic blood to be clinically relevant as meta-analyses of randomized trials show that such a reduction can reduce the risk of CVD by about 10% regardless of CVD history, including among people with normal to high-normal blood pressure [22], as well as specifically in middle-aged adults [23].

Based on systolic blood pressure data in Stockholm Region that were obtained from electronic medical records, the estimated variance of systolic blood pressure levels between PCCs (clusters) was equal to 2, and the variance between subjects within PCCs (individuals) was equal to 256. These settings give rise to the underlying variance structure of the data, essential for sample sizes calculations, namely a difference of 5 mmHg in systolic blood pressure between arms (VA = 12.5), variance between clusters, (VC = 2), and variance between individuals within PCCs (VE = 256). We calculated the number of clusters, the number of individuals, and the power of the sample using various combinations of VA, VC, and VE values close to those outlined above. For each calculation, we adjusted one parameter while holding the other two constant. We used the package clusterPower version 0.7.0 [24], R Statistical Software version 4.1.3 [25], for the sample size and/or power calculations for the different variance settings.

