Accordingly, we calculated that based on 15 clusters in each arm, a minimum of 840 participants (*n* = 420 in each arm and *n* = 28 per cluster) would yield 80% power to detect a reduction of 5 mmHg systolic blood pressure in the HDI group as compared to OS. Rising power to 90% while keeping the number of clusters to 15 per arm would require a minimum of 1200 participants (*n* = 600 in each arm and *n* = 40 per cluster). Additionally, anticipating difficulties with cluster recruitment and retention, we also calculated that if the size of the cluster is increased to *n* = 69, a power of 80% would be obtained with 9 clusters per arm, and 90% power would be obtained with 11 clusters per arm. Because we expected difficulties with recruitment of PCCs and participant recruitment within PCCs, as well as subsequent attrition of the two, the goal was to recruit at least 30 PCCs (*n* = 15 in each arm) in Stockholm Region, each of which will aim to recruit *n* = 100 participants, yielding a maximum total study population of *N* = 3000.

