### Statistical analysis

Baseline characteristics in the two arms will be described by means of typical summary measures e.g., means, medians, frequencies, proportions, standard deviations, quartiles, and counts. Characteristics of dropouts will be explored in comparison to non-dropouts.

The core tool of outcome analysis will be a hierarchical model consisting of two levels, individuals and PCCs. The primary model for analyzing changes in systolic blood pressure (primary outcome), other biological risk factors, lifestyle habits, and HRQoL over 6 and 12 months will be a mixed-effects generalized linear model (GLM) to capture variability between and within PCCs. Following the GLM framework, the assumptions concerning the underlying probability distribution and the link function (the way the expected value of the outcome is related to a set of independent variables and their associated effects) will differ between continuous, binary, categorical, and count outcomes. In these models, the treatment effect (HDI versus OS) will be assessed using a fixed effect represented by a dummy variable at PCC level, specifying the type of treatment (HDI/OS). Together, this enables the estimation of the average treatment effect, while accounting for the hierarchical structure of the data. We will estimate unadjusted effects and effects adjusted both/either at the individual level and PCC level, e.g., adjusted for demographic characteristics, socioeconomic status, CNI level, and baseline values of the referred outcome. The analyses will be conducted on an intention-to-treat basis and will be carried out using the *glmer* function of the *lme4* package under the R platform [47]. Potential effect modification will be explored through subgroup analyses and interaction analyses considering sex, birth country, and socioeconomic characteristics. A sensitivity analysis will be conducted to assess whether the individual randomization of a single PCC introduced bias. Thus, we will perform analyzes both including and excluding this PCC. The occurrence of missing data will be dealt with accordingly.

For the assessment of T2D and CVD incidence and mortality during the extended 5 and 10 years of follow-up, we will calculate hazard ratios using a mixed-effect Cox regression model and packages *survival* and *coxme* under the R platform [48–50]. We will also calculate the number needed to treat (NNT).

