#### Health economic evaluation

For the short-term health economic evaluation, a healthcare costing perspective will be used, including utilization of healthcare in primary, specialized outpatient, and inpatient care as well as medication. Data from the VAL database will be used for this analysis. Total health resource use and associated costs in each arm will be accumulated and analyzed over the 12-month follow-up. Net costs, which is the difference between intervention costs and total health resource use of participants, will thereafter be estimated for both arms. Total QALYs at 6 and 12 months in each arm will be calculated by using the area under the curve method [51]. Incremental differences in QALYs and costs between participants in the HDI and OS arm at 6 and 12 months will be assessed using GLM models with gamma distribution for cost outcomes and gaussian for QALYs. Logistic regression analyses will be used for estimating between-group differences in persons with blood pressure target attained. Between-group differences in healthcare costs will be analyzed while controlling for baseline costs, while baseline utilities will be controlled for in analyses of accumulated QALYs between groups. The cost per QALY and per blood pressure target attained will be assessed using the incremental differences between the groups at 12 months.

For the long-term assessment of cost-effectiveness, total healthcare resource use and its associated costs will be accumulated and analyzed over the 5- and 10-year follow-up period, employing the same data source (VAL) and analytical framework (GLM) as for the short-term assessment. Intervention costs will also be used in this evaluation for the estimation of net costs. Incident cases of T2D and CVD will similarly be accumulated over the follow-up period, and incremental differences at 5 and 10 years will be assessed using logistical analyses. The total costs and health outcomes will be analyzed in a cost-consequence analysis. Furthermore, accumulated deaths due to T2D and CVD over the 5- and 10-years follow-up will be used to assess incremental life years gained between the two groups, and this outcome measure will consecutively be used in a cost-effectiveness analysis estimating the cost per life years gained. Probabilistic sensitivity analyses will be employed throughout the short- and long-term analyses to account for parameter uncertainty.

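### The economic models name no allowance for the primary care centre; fitted as written, with a positive ICC, their intervals would be too narrow

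*Protocol article*

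**What the plan says.** Under Study design and setting, the protocol article states: "The PCCs represent the clusters and unit of randomization".

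The Statistical analysis section opens with a two-level model, individuals within PCCs, as the main tool of outcome analysis. For systolic blood pressure, the other biological risk factors, lifestyle habits and health-related quality of life, the primary model "will be a mixed-effects generalized linear model (GLM) to capture variability between and within PCCs". Incidence and mortality at 5 and 10 years get a mixed-effect Cox model.

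The subsection Health economic evaluation names its own models:

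- Differences in QALYs and costs "will be assessed using GLM models with gamma distribution for cost outcomes and gaussian for QALYs". The only covariates named are baseline costs (for costs) and baseline utilities (for QALYs).
- For target attainment: "Logistic regression analyses will be used for estimating between-group differences in persons with blood pressure target attained".
- For the long term, costs use the same GLM framework, and for accumulated cases of type 2 diabetes and cardiovascular disease "incremental differences at 5 and 10 years will be assessed using logistical analyses".
- Probabilistic sensitivity analyses are to cover parameter uncertainty throughout. Their inputs are not described.

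The subsection mentions no random effect, cluster-robust variance, estimating-equation approach or cluster bootstrap.

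**The concern.** Participants of one PCC share staff, referral habits and a neighbourhood, so their costs and outcomes may be correlated. The treatment is assigned to the whole PCC. A model that treats participants as independent leaves the between-PCC variance out of the standard error of the arm difference.

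The article says mixed-effects where it describes the clinical and survival models, and it does not say so for the economic ones. Two outcomes thereby meet two descriptions. Target attainment derives from the same blood pressures that the main section models with PCC variability. Incident cases get a mixed-effect Cox model in one place and logistic analyses with no PCC level in the other.

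Specific aims V to VII (resource use and costs, cost per QALY and per blood-pressure target attained, cost per life year gained) draw on this subsection, and the Discussion expects the trial to inform the decision on scale-up. If standard errors that ignore the PCC also fed the probabilistic sensitivity analysis, the cost-effectiveness results would look more certain than they are.

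**Working it through.** **Inputs from the protocol article.** The Sample size section gives the blood pressure variances: "variance between clusters, (VC = 2), and variance between individuals within PCCs (VE = 256". The effect is "a difference of 5 mmHg in systolic blood pressure between arms (VA = 12.5", and 12.5 = 5²/2. Cluster sizes in the same section are 28, 40 and 69 in the power scenarios and 100 as the recruitment target per PCC, which gives the stated maximum of 3000.

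**The plan's own figure.** No figure is stated for the economic analyses. The power figures show that the variances above were used with clustering included. The protocol states "based on 15 clusters in each arm, a minimum of 840 participants" for 80% power, at 28 per cluster. I used a cluster-level t-test with 2(k − 1) degrees of freedom, two-sided 5% (assumed) and SE = √(f × 2 × (VC + VE/m)/k):

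- k = 15, m = 28, f = 2: SE = √(4 × (2 + 9.143)/15) = 1.724, power 79.95% (stated 80%).
- k = 15, m = 40, f = 2: SE = √(4 × (2 + 6.4)/15) = 1.497, power 89.7% (stated 90%).
- m = 69, f = 2: the smallest k is 9 for 80% (83.8%) and 11 for 90% (91.0%), as stated.

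The figures therefore reproduce with f = 2, the doubled variance of a change score with no correlation between baseline and follow-up. The article does not state that factor, and it has no bearing on this point. With f = 1, power at 15 × 28 would be 97.7%.

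**Effect of leaving out the PCC level.**

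- ICC = VC/(VC + VE) = 2/258 = 0.00775
- Design effect: DE = 1 + (m − 1) × ICC
- Correct SE / naive SE = √DE, so naive width / correct width = 1/√DE
- Coverage of a naive 95% interval = 2Φ(1.96/√DE) − 1

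At m = 28: DE = 1 + 27 × 0.00775 = 1.21, √DE = 1.10, coverage 92.5%.
At m = 100: DE = 1 + 99 × 0.00775 = 1.77, √DE = 1.33, relative width 0.75, coverage 86%.

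| ICC | Source | Per PCC | DE | SE ratio | Naive/correct width | Naive coverage |
|---|---|---|---|---|---|---|
| 0.00775 | protocol, blood pressure | 28 | 1.21 | 1.10 | 0.91 | 92.5% |
| 0.00775 | protocol, blood pressure | 40 | 1.30 | 1.14 | 0.88 | 91.4% |
| 0.00775 | protocol, blood pressure | 69 | 1.53 | 1.24 | 0.81 | 88.7% |
| 0.00775 | protocol, blood pressure | 100 | 1.77 | 1.33 | 0.75 | 86.0% |
| 0.01 | assumed | 28 | 1.27 | 1.13 | 0.89 | 91.8% |
| 0.01 | assumed | 100 | 1.99 | 1.41 | 0.71 | 83.5% |
| 0.02 | assumed | 28 | 1.54 | 1.24 | 0.81 | 88.6% |
| 0.02 | assumed | 100 | 2.98 | 1.73 | 0.58 | 74.4% |
| 0.05 | assumed | 28 | 2.35 | 1.53 | 0.65 | 79.9% |
| 0.05 | assumed | 100 | 5.95 | 2.44 | 0.41 | 57.8% |

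The formulas assume equal cluster sizes and a normal approximation. They use the ICC that remains after adjustment for the baseline covariate.

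**The case against.** The best answer is that the subsection does not stand alone. It lies under Statistical analysis, whose opening makes a two-level model the core tool. That section introduces the abbreviation GLM directly after the words for a mixed-effects generalized linear model, and says that distribution and link will vary with the type of outcome. Gamma for costs and gaussian for QALYs can be read as that choice. QALYs and target attainment also come from quality of life and blood pressure, both assigned to the mixed model. A condensed article may leave the random-effect structure of an economic evaluation to a fuller document.

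This has weight. A reader might infer that the protocol prescribes ordinary regression with the PCC level excluded, and that the intervals will therefore be wrong. The text does not say that: it is silent on the PCC level and never rules it out.

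The answer does not settle the matter, however. The abbreviation list expands GLM without mixed effects. Costs appear in neither list of outcomes given a mixed model. The abstract ties the mixed models to health outcomes and describes the economic evaluation in a separate sentence. The shorthand reading also does not reach the logistic analyses, which are not called GLM. Since the subsection does commit to model family, distribution and covariates, an analyst who follows it literally would leave out the PCC.

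Three further limits are fair:

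- 100 per PCC is the maximum, and the protocol expects recruitment difficulty and attrition.
- No ICC is given for any economic outcome.
- The article plans no hypothesis test for the economic results, so interval coverage is a better measure of the harm than a type I error rate.

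**Conclusion.** The point holds in conditional form. As written, the economic models carry no allowance for the randomisation by PCC, unlike the clinical and survival models. If they are fitted that way and the ICC is positive, the intervals for cost, QALY and target-attainment differences would be too narrow, and so would those for 5- and 10-year case differences.

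Using the blood pressure ICC only as an illustration, the loss is modest at 28 per PCC and material at the recruitment target of 100, where a quarter of the correct width is missing. The coverage figures for ICCs of 0.01 to 0.05 rest on assumption alone.

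It is tempting to add that costs cluster more strongly than blood pressure because they depend on how a PCC is run. The documents do not show this. Public and private PCCs are funded and governed under the same rules, and the costs include specialised outpatient and inpatient care and medication. Nor do they say that the probabilistic sensitivity analysis would take its inputs from unclustered standard errors; its inputs are simply not described.

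The primary outcome analysis is unaffected. The clarification should nevertheless be made before the economic analysis is run.

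**What to change.** State in Health economic evaluation that the two-level structure of the Statistical analysis section also applies there: a PCC random intercept in the gamma, gaussian and logistic models, for the 12-month and the 5- and 10-year analyses.

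Alternatively, specify a two-stage bootstrap that resamples PCCs and then participants within them, with each participant's cost and QALY kept together so that their correlation is preserved.

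In either case, say that the probabilistic sensitivity analysis is based on these cluster-aware estimates, and report the estimated ICCs for costs, QALYs and target attainment.

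The change needs no new data and no further recruitment. It costs some added wording, slightly more computing and wider intervals.

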### Recruitment of participants, eligibility criteria, and informed consent

Patients aged 50–59 years old who are enlisted at the participating PCCs will be considered eligible for invitation to participate in the trial. Each of the PCCs will be asked to invite and enroll patients until they have reached *n* = 100 participants. For PCCs randomized to HDI, a healthcare professional (registered nurse or general practitioner) from the PCC will send a letter by mail to eligible patients, providing brief information about the intervention and a scheduled date and time for a phone call. During the phone call, the healthcare professional will provide more information about the intervention and the potential participant will have the opportunity to ask questions. Previous research indicates that this approach (information by ordinary mail followed by a phone call) could increase attendance rates compared to a mail-only invitation [26, 27]. If the patient expresses an interest in participating, an appointment for the screening and the health dialogue will be scheduled. Based on all enlisted patients, the healthcare professional will invite patients consecutively based on alphabetical order of their surnames. Patients choosing to participate will provide written informed consent and have the possibility to withdraw their participation at any time without the need to state a reason (Additional file 2). As part of the participant information and informed consent, participants are made aware that the trial is designed to evaluate how well HDI and OS can detect biological risk factors (surrogate endpoints) for T2D and CVD (target outcomes) and whether they lead to reduced risk of T2D and CVD in the long-term.

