For PCCs randomized to OS, eligible patients will be identified upon scheduling an appointment at their PCC for any reason, except for those whose scheduled appointments are related to hypertension, T2D, and CVD, or acute events requiring immediate care or immediate referral. Upon scheduling the appointment, the healthcare professional (assistant nurse, registered nurse, or general practitioner) will provide brief information about the trial. Next, once the patient arrives for their visit, they will again be given information about the trial. If agreeing to participate, they will provide written informed consent and have the possibility to withdraw their participation at any time without the need to state a reason (Additional file 3). Figure 2 shows the timeline of the study, including timepoints for enrollment, allocation, and assessments, as per SPIRIT guidance.

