### Process and implementation outcomes

Process and implementation outcomes will be assessed 6 months post intervention according to Proctor et al.’s taxonomy [41]. Adoption will be measured as the number of invited PCCs that agree to participate in the study. Healthcare professionals’ perceptions of how acceptable, appropriate, and feasible the interventions are to implement within the context of the PCCs will be assessed using the Acceptability of Intervention Measure, the Intervention Appropriateness Measure, and the Feasibility of Intervention Measure [42]. The measures consist of four items each and responses are reported on a 5-point Likert scale ranging from “completely disagree” to “completely agree.” Fidelity will be operationalized as adherence to the original intervention protocols and assessed using data from electronic medical records. For the HDI, we will report to what extent (proportion) all parameters of the screening have been assessed and whether the following health dialogue has been conducted, as based on documentation in the patients’ electronic medical records. For the OS, we will assess to what extent (proportion) all parameters of the screening have been assessed and to what extent that identification of an elevated risk factor has resulted in measures taken according to existing clinical practice guidelines. (For example, what proportion of participants who report daily smoking are given brief advice about smoking cessation and asked whether they want a referral to a qualified tobacco cessation advisor.) Penetration will be assessed in terms of the proportion (in both arms) of patients choosing to participate among those invited (attendance rate), and the reasons for declining participation among non-participants. We will also report (in both arms) the representativeness of participants as compared to the total eligible population based on socioeconomic characteristics. Participants data on sex, level of education, occupation, annual income, and birth country will be compared to that of the total eligible population, using data from the Longitudinal Integration Database for Health Insurance and Labour Market Studies (LISA) [43]. LISA is managed by Statistics Sweden (the agency of government statistics), which has a 100% coverage for all Swedish citizens aged > 16 years since 1990 and for all aged > 15 years since 2010. In Stockholm Region, the data from LISA is already integrated with the VAL database and used routinely. Additionally, we will assess case-finding rates (in both arms) defined as the proportion of participants where elevated levels of T2D and CVD risk factors are detected for the first time, e.g., the proportion of participants with prediabetes defined as a fasting blood glucose of 6.1–6.9 mmol/l and hypertension defined as blood pressure of ≥ 140/90 mmHg. Finally, semi-structured interviews will be conducted with one healthcare professional and potentially one manager from each participating PCC, with the aim of exploring barriers to and facilitators for implementation of the interventions. The interviews will be audio-recorded, transcribed verbatim, and analyzed using deductive content analysis [44]. The Consolidated Framework for Implementation Research will be used to guide the analysis [45]. Costs related to implementing and running HDI and OS will be analyzed using a bottoms-up, micro-costing approach. This includes staff training, time spent delivering the interventions, necessary materials, IT-infrastructure, etc.

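### The economic evaluation names baseline control for costs and QALYs but none for blood pressure target attained, leaving the denominator of the cost per target attained exposed to baseline case mix

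*Protocol article*

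**What the plan says.** Aim VI (Objectives) includes a short-term cost per blood pressure target attained. Health economic evaluation gives the method: "Logistic regression analyses will be used for estimating between-group differences in persons with blood pressure target attained". The next sentence assigns baseline covariates: "Between-group differences in healthcare costs will be analyzed while controlling for baseline costs, while baseline utilities will be controlled for in analyses of accumulated QALYs". No baseline covariate is assigned to the blood pressure model. The estimates are then used as follows: "The cost per QALY and per blood pressure target attained will be assessed using the incremental differences between the groups at 12 months".

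The recruitment section sets who is in the analysis. Entry needs only age and enlistment: "Patients aged 50–59 years old who are enlisted at the participating PCCs will be considered eligible for invitation to participate in the trial". In the health dialogue arm, "Based on all enlisted patients, the healthcare professional will invite patients consecutively based on alphabetical order of their surnames". In the opportunistic screening arm, patients are identified when they book a visit, "except for those whose scheduled appointments are related to hypertension, T2D, and CVD, or acute events requiring immediate care or immediate referral".

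Two general statements bear on adjustment. Statistical analysis plans both unadjusted and adjusted effects for the mixed models of biological risk factors, lifestyle habits and quality of life, with covariates given as examples: "e.g., adjusted for demographic characteristics, socioeconomic status, CNI level, and baseline values of the referred outcome". The Discussion concedes selection bias of unpredictable direction, because unblinded participants are recruited after randomization, and promises covariate adjustment in general terms without naming a covariate for any particular model.

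**The concern.** Being at a blood pressure target at 12 months depends strongly on blood pressure at entry. If the arms differ at entry, an unadjusted comparison of attainment carries that difference into the result.

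Here there is a reason to expect that the arms may differ. One arm invites from the whole list, including people already followed for hypertension. The other draws on people who attend, and leaves out visits made for hypertension, type 2 diabetes or cardiovascular disease. The two filters relate to blood pressure differently.

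The stake is a ratio. Incremental attainment is its denominator, so an error of a few percentage points there changes the cost per target attained by a much larger relative amount. The section already guards the cost and QALY comparisons against this kind of baseline difference, while the third effect measure in the same paragraph has no named guard. Baseline systolic pressure is measured in both arms.

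**Working it through.** The plan gives no figure for target attainment, so there is none to reproduce. The check asks how far a baseline difference could move attainment, compared with the effect the trial is planned around.

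**Inputs from the protocol (Sample size; Randomization and blinding)**
- Variance between centers 2, within centers 256. Total SD = √(2 + 256) = √258 = 16.06 mmHg.
- Planned effect 5 mmHg.
- 16 centers per arm, aiming at 100 participants each.

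**Assumptions, because the protocol does not give them**
- Systolic pressure is roughly normal, with mean 130 mmHg (range shown: 125 to 135).
- The target is systolic pressure below 140. The only threshold in the document is for case-finding, "hypertension defined as blood pressure of ≥ 140/90 mmHg", and it is borrowed for illustration only.
- The baseline difference persists in full to 12 months.

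**Formula.** Share at target = Φ((140 − mean)/16.06).

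**At mean 130**
- At entry: Φ(10/16.06) = Φ(0.623) = 73.3%.
- Mean lower by the planned 5 mmHg: Φ(15/16.06) = Φ(0.934) = 82.5%. Effect: 9.2 points.
- No effect, one arm 2 mmHg lower at entry: Φ(12/16.06) = Φ(0.747) = 77.2%. Spurious difference: 3.9 points, or 3.9/9.2 = about 42% of the planned effect.

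**Across assumed means**

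| Assumed mean | At target at entry | 5 mmHg effect | Persistent 2 mmHg baseline difference, no effect |
|---|---|---|---|
| 125 | 82.5% | 6.9 points | 3.0 points |
| 130 | 73.3% | 9.2 points | 3.9 points |
| 135 | 62.2% | 11.1 points | 4.6 points |

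If only 60% of the 2 mmHg carries to 12 months (1.2 mmHg), the shift at mean 130 is Φ(11.2/16.06) − Φ(10/16.06) = 2.4 points.

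**What this does to the ratio (mean 130, true effect 5 mmHg, incremental cost held fixed)**
- Health dialogue arm 2 mmHg higher at entry: net difference 3 mmHg, Φ(13/16.06) − 73.3% = 79.1% − 73.3% = 5.8 points. Cost per target attained is multiplied by 9.2/5.8 = 1.6.
- Health dialogue arm 2 mmHg lower at entry: net difference 7 mmHg, Φ(17/16.06) − 73.3% = 85.5% − 73.3% = 12.2 points. Cost per target attained is multiplied by 9.2/12.2 = 0.75.

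**Can chance produce such a difference?** The standard error of the baseline difference in means is √(2 × (2/16 + 256/1600)) = √(2 × (0.125 + 0.160)) = √0.57 = 0.75 mmHg, so the 95% chance range is about ±1.5 mmHg. A 2 mmHg difference is about 2.6 standard errors, and 3 mmHg about 4. At the smaller design of 15 centers of 28 per arm, the standard error is √(2 × (2/15 + 256/420)) = 1.2 mmHg. At full recruitment, chance is therefore a minor source, and a difference of 2 mmHg or more would point to differential enrolment.

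**The case against.** The strongest reply is that adjustment is already planned. The Statistical analysis section covers systolic pressure, allows for binary outcomes, and lists the baseline value of the outcome among possible covariates; the Discussion promises covariate adjustment for imbalance. A reader might infer from the economic section that the target model will not be adjusted. The document does not say that: it is silent for this model, and silence is not exclusion. That part of the objection stands. It does not settle the matter, because the baseline value is only an example there, beside unadjusted effects, and the Discussion names no covariate. The economic section sets its own covariates outcome by outcome, and restates the one for utilities even though quality of life already falls under the general clause.

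A second reply is that the target and its population may be set in an analysis plan that is not shown. This also stands, so the missing definition is no part of the point. A reader might infer that everyone at target on entry will count as having attained it. That is the natural reading of the wording, but the text does not fix it.

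Third, a reader might infer that the ratio mainly reflects who was enrolled, since under the assumptions above most people are at target on entry. This does not follow. The ratio uses the difference between arms, and people at target on entry largely cancel when the arms are balanced. Enrolment would dominate only if the baseline shift approached the treatment effect.

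Fourth, the share of all participants at target is a legitimate outcome in a prevention trial of an unselected age group. That stands, and nothing here asks for it to be replaced.

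**Conclusion.** The point holds in a limited form. For the one effect measure in the short-term economic analysis that rests on blood pressure, the protocol states no baseline control, while stating it for the other two. Because of open eligibility, different enrolment routes and the conceded selection bias, the denominator of the cost per target attained is materially exposed to baseline case mix.

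The size is illustrative. It rests on an assumed mean, an assumed target, normality and full persistence of the baseline difference; only the SD, the 5 mmHg effect and the center numbers come from the protocol. The 2 mmHg is a what-if value: the opportunistic screening rule excludes appointments, not hypertensive patients as such, so neither the size nor the direction of any imbalance can be derived from the document. The supportable conclusion is that a modest imbalance would matter, not that one will occur. A secondary, economic result is affected; the primary outcome analysis is not.

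**What to change.** In Health economic evaluation, extend the sentence on baseline controls to say that the target-attainment model adjusts for baseline systolic pressure as a continuous covariate, in line with the Statistical analysis framework and the controls already named for costs and utilities. State that the adjusted risk difference, obtained by standardising the model's predictions over all participants, is the denominator of the cost per target attained; a logistic coefficient does not supply that difference directly.

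As an optional supporting display, report attainment among participants above target at baseline. That group is smaller, so its estimate is less precise, and it answers a different question from the all-participant result.

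The cost is wording only. Baseline blood pressure is already collected in both arms, so no new data are needed. Adjustment deals with the difference in measured baseline pressure; it does not remove selection on unmeasured factors, and the Discussion's caveat should stay.
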